## Abstract

**Background:**

Non-erosive reflux disease (NERD) is characterized by typical gastroesophageal reflux symptoms, such as heartburn and regurgitation but an absence of esophageal mucosal damage during upper gastrointestinal endoscopy. Although proton pump inhibitors (PPIs) are the first line therapy, almost 50% of patients with NERD fail to respond to this treatment. Traditional Chinese medicine (TCM) can better relieve the symptoms of NERD. Therefore, a randomized controlled trial (RCT) was designed to investigate the efficiency of TCM granules based on Tongjiang (TJ) methodology combined with PPI step-down therapy for NERD patients who did not respond to PPIs alone.

**Method:**

This multicentered, double-blinded, RCT with two parallel groups will recruit 174 participants who will be randomized into the TCM granules combined with PPI step-down group (*n* = 87) and the TCM granules placebo combined with PPI step-down group (*n* = 87). Both groups of participants will receive 6 weeks of treatment and 4 weeks of follow-up, and all participants will be assessed for related symptoms, mental health status, and quality of life at each visit. The primary outcome measurements include visual analog scale (VAS) for heartburn and regurgitation and the major symptoms scale. The secondary outcome measurements include PPI withdrawal rate, symptom recurrence rate, minor symptoms scale, SF-36, PRO, SAS, SDS, GERD–HRQL, and TCM syndromes scales.

**Discussion:**

Previous research has shown that TCM is capable to alleviate NERD symptoms. This trial will help to provide a better understanding of the synergistic efficiency of the combination of TCM and PPIs, to explore whether the dosage of PPIs can be reduced after the supplement of TCM granules and to provide a feasible plan to reduce dependencies or withdraw NERD patients from PPIs. The outcome of this trial is expected to reduce the symptom recurrence rates, lessen patients’ physical and psychological burdens, and achieve good social benefits.

**Trial registration:**

Clinicaltrials.gov NCT04340297. Registered on April 9, 2020

## Background

Gastroesophageal reflux disease (GERD) is one of the most common chronic progressive upper gastrointestinal tract disorders of the esophagus, characterized by heartburn and regurgitation symptoms [1]. The prevalence of this disease ranges from 2.5% to more than 25% according to individual cross-sectional surveys [2]. GERD can be divided into several phenotypes: erosive esophagitis (EE), non-erosive reflux disease (NERD), and Barrett’s esophagus (BE) [3, 4]. NERD is the most frequent phenotype of gastroesophageal reflux disease (GERD). Rome IV consensus defines NERD as “the presence of abnormal acid exposure time (AET) with or without reflux–symptom association on ambulatory reflux monitoring performed off anti-secretory therapy” [5]. It accounts for approximately 70% of GERD patients and is characterized by typical symptoms and the lack of any visible endoscopic findings of esophageal mucosal lesions [6, 7]. The majority of patients with NERD have weakly acidic reflux [8]. Some studies have shown that the function of the esophageal mucosal barrier is not significantly altered in NERD patients [9]. NERD is a refractory gastrointestinal disease, and patients often need long-term treatment to control their symptoms. Proton pump inhibitors (PPIs), a type of acid-suppressive drug, are considered the first-line treatment drugs for NERD. There are obvious deficiencies in treatment guideline and safety of PPIs, which demonstrated the following problems in clinical practice: approximately 50% of patients with weakly acidic reflux respond partially or not at all to PPIs [10]; 20–30% of patients treated with a standard PPI dose for troublesome GERD symptoms experience persistent heartburn and/or regurgitation [11, 12], and more than 75% NERD patients may experience symptomatic relapse within 6 months of stopping treatment so they receive long-term treatment to control symptoms [13, 14]; long-term use of PPIs can cause many adverse events, such as indigestion, fundic gland polyps, atrophic gastritis, and gut microbiota imbalance [15, 16], as well as PPI resistance or dependence. This life-long dependency leads to a huge psychological and physical burden for the patient [17].

Due to insufficient patient-response-to treatments and various undesirable negative side effects, more and more scientific researchers in the medical area have begun to consider PPI step-down therapy in recent years. PPI step-down therapy means gradually reducing dosage and patients’ dependence on PPIs according to the outcome and symptoms changes of patients. Multiple strategies may be used to de-escalate (i.e., stop or reduce) PPIs, including abrupt PPI withdrawal, step down therapy, and H_2_ blocker (i.e., famotidine) substitution. However, one randomized controlled trial (RCT) study showed that about 68% patients experienced symptom recurrence after discontinuation of long-term PPI therapy [18], thus, meaning that stopping PPIs is not sufficient to control patients’ symptoms in a long-term period.

The use of complementary and alternative approaches has proven to have an effect on the treatment of NERD [19, 20]. In recent years, numerous studies have evaluated the clinical effectiveness of traditional Chinese Medicine (TCM) herbals for the treatment of NERD. A review article showed that in addition to their acid-suppressive properties, anti-inflammatory, and antioxidant activity of the herbal remedies, these herbal medicine seem to provide a safer and more effective treatment compared to their pharmaceutical drug counterparts. Herbal remedies used in human studies have led to the alleviation of heartburn and regurgitation related to NERD where PPI treatment has failed to show a promising effect. Moreover, herbal remedies appeared to have a longer-lasting therapeutic effect than conventional anti-secretory agents have [19]. A systematic review has reported that the total effective rate of TCM alone was superior to single PPIs or prokinetics for their clinical efficacy. TCM also has advantages in reducing recurrence rate and adverse events like constipation, faint headache experience, and nausea [21]. Although TCM has been examined for its ability to alleviate PPI-refractory symptoms, including the reduction of recurrence of these symptoms as well as improve the quality of life of patients, a high-level evidence-based support and thorough understanding of the underlying mechanisms of the action of TCM herbal remedies were lacking [22].

Tongjiang (TJ) methodology is used in TCM to treat functional gastrointestinal diseases. TJ literally means unobstructed and descent, and the main goals of TJ methodology in TCM are to regulate visceral dysfunction, adjust the imbalance between internal and external energies, restore the physiological functions of the viscera, and revitalize the mind, spirit, and body for a holistic well-being balance. Herbal granules based on TJ methodology can help regulate cell-to-cell tonic equilibrium and improve the overall Qi and food passing unimpeded through the entire gastrointestinal tract. Prior to this trail, we have performed an RCT study on the efficacy of TJ granule to improve the quality of the results and to provide estimates for further sample size calculation. The results showed that TJ granule could improve the symptoms which included heartburn, chest pain, acid or bitter tastes in mouth, and nausea. On the quality of life, it could also improve the domains of physical functioning and general health, and no adverse event was found [23].

For most common patients presented with NERD [17], we will use TCM granules based on the TJ methodology in cooperation with PPI step-down therapy to treat NERD. We designed this rigorous multicenter, double-blinded, RCT using TJ methodology granules with PPI step-down therapy for NERD patients with regard to NERD-related symptoms and symptom distress, to explore its therapeutic efficiency, measure recurrence rate, understand the mechanisms of the therapy, and estimate PPI withdrawal rate.

We aimed to independently examine the efficiency and safety of TJ methodology granules combined along with PPI step-down therapy for NERD patients with regard to NERD-related symptoms and symptom distress. The primary objective is to develop a new therapy for the treatment of NERD, to obtain high-level evidence-based medical evidence. The secondary objective is to evaluate the advantages of the new therapy, hoping to solve the problems of side effects and dependence caused by long-term use of PPIs. The last objective is to explore some of the mechanisms based on observations of the changes in patients’ gut microbiota.

## Method

### Study design

This trial will adopt a multicenter, double-blinded, randomized controlled trial with two parallel groups, to explore the efficiency of the TJ methodology granules combined with PPI step-down for NERD. The protocol will be described in accordance with Recommendations for Interventional Trials 2013 guidelines [24]. The details of the study design are shown in Fig. 1.

**Fig. 1 Fig1:**
[figure not shown]
Flowchart of the proposed trial. VAS, visual analog scale; TCM, traditional Chinese medicine; SF-36, the MOS 36-item Short From Health Survey; PRO, patient-reported outcome; SAS, Self-Rating Anxiety Scale; SDS, Self-Rating Depression Scale; GERD-HRQL, the Gastroesophageal Reflux Disease-Health-Related Quality-Of-Life

### Study setting

This multicenter, double-blind, RCT will be conducted at six hospitals in China (Xiyuan Hospital of China Academy of Chinese Medical Sciences; Guangdong Provincial Hospital of Traditional Chinese Medicine; Wuhan No.1 Hospital; The First Affiliated Hospital of Tianjin University of Traditional Chinese Medicine; Traditional Chinese Medicine Hospital of Kunshan; Liuzhou Hospital of Traditional Chinese Medicine). These six hospitals are all qualified to conduct clinical studies and relevant experience. A total of 174 participants will be recruited from the hospital outpatient departments, hospital websites, and posters. Participants will be divided into three groups according to their different TCM syndromes, and those with the same syndrome will be divided into the intervention group and the control group at a 1:1 ratio.

### Eligibility criteria

All participating patients must first be judged by TCM physicians to determine whether they meet the following inclusion and exclusion criteria.

#### Inclusion criteria

The following are the diagnostic criteria of NERD according to the *China Consensus Opinion on Gastroesophageal Reflux Disease, 2014 edition*: (1) patients with typical heartburn and regurgitation that negatively affect the patient’s quality of life, mild symptoms for ≥ 2 days; (2) GERD Q scale score ≥ 8 points; and (3) NERD is diagnosed when there is no damage to the esophageal mucosa on gastroscopy within 1 month, esophageal 24-h pH, and impedance monitoring for pathological reflux within 1 year, and reflux esophagitis, Barrett’s esophagus, functional esophageal disease, and other upper gastrointestinal diseases are excludedThe diagnostic criteria of stagnation of liver and stomach heat syndrome or spleen deficiency and dampness-heat syndrome intermingled heat and cold syndrome in TCM. Major symptoms: (1) heartburn and (2) regurgitationTreatment with PPIs for more than 8 weeks and whose curative effect is not satisfactoryAgreement to participate in the clinical trial and sign the informed consent formAge from 18 to 65 years old

#### Exclusion criteria

Pregnant or breastfeeding females or those who are planning pregnancyOther chronic GI diseases like RE or BE or primary diseases such as peptic ulcers, achalasia, pyloric obstructions, and esophageal cancer that can cause gastroesophageal refluxSevere cardio-cerebrovascular system diseases, liver, kidney, hematopoietic system diseases, psychiatric diseases, and tumorsAnti-reflux surgery (fundoplication or endoscopic minimally invasive surgery) and other upper gastrointestinal surgery recordsHistory of allergies or drug and food allergies appearing during the trialsInability to describe self-symptoms or to cooperate with treatmentAbuse of alcohol or drugs, frequent changes in the working environment and tendency to dropoutParticipation in other clinical trials within 4 weeks

#### Dropout criteria

Decision to exit the trial himself/herselfLoss to follow-upPoor complianceDiagnosis with other TCM syndromes or an order to withdraw by the TCM physicians

For the occurrence of patients presented with the above situation, we will consider making a suspension. In cases of dropout, the reason should be explained. If there are baseline pharmacodynamic data, the last main therapeutic effect index can be transferred to the final results for statistical analysis, and the CRF should be retained.

### Intervention

Each center’s treatment of participants will be provided by licensed TCM physicians. TCM physicians will distribute granules to participants tailored according to their symptoms under the guidance of the TJ methodology. To reduce intervention bias, TCM physicians have conducted relevant training. Our record physicians must study and be familiar with the scales and questionnaires in this trial and learn the skills to guide participants to complete them appropriately. The granule-distributing physicians arrange and distribute the granules accordingly. In addition to that, we have a chief physician responsible for overseeing the entire process.

#### Intervention group

Based on the curative effect of treating NERD in clinical practice, we selected three kinds of TCM granules based on TJ methodology. According to the different TCM syndromes, participants with stagnation of liver and stomach-heat syndrome will be treated with Tongjiang (TJ) granule, those with spleen deficiency and dampness-heat syndrome will be treated with Jianpiqinghua (JQ) granule, and those with intermingled heat and cold syndrome will be treated with Wenpiqingwei (WQ) granule. These herbal granules are available from the Xiyuan Hospital as an in-hospital preparation. TCM granules are concentrated herbal particles obtained by the mean of spray drying the hot water extract of a mixture of raw herbs. TCM granules are extracted with water to make an aqueous extract or decoction used for treatment. Each bag of granules (approximately 20 g) will be dissolved in 200 ml water and taken twice a day, 1 h after meal. Participants in all three groups cooperated with PPI step-down therapy. From week 1 to week 2 of treatment, the dose of PPIs will be half of the original dose, once a day, taken before bedtime. The PPIs will be replaced with famotidine 20 mg from week 3 to week 4, taken before bedtime. From week 5 to week 6, acid-suppressive drugs will be withdrawn, and only TCM granules will be administered. There will be 6 weeks of treatment and 4 weeks of follow-up.

#### Control group

Patients will be treated with the corresponding TJ methodology granules placebo. The placebo granules consist of cyclodextrin and 5% real TJ theory granules to imitate the color and smell of the real counterpart. Both herbal granules and placebo are manufactured by China Resources Sanjiu Medical and Pharmaceutical Co., Ltd. (Hefei, China; Batch number: 2004902) according to the standards of the Good Manufacturing Practice. The physical properties of the placebo, such as appearance, size, color, dose form, weight, taste, and smell, will be similar to those of the TCM granules. The PPI step-down therapy will be the same as that for the intervention group.

### Cointerventions

One week prior to the start of treatment, patients will be required to stop their intake of other drugs related to TCM therapies of NERD; however, acid-suppressive drugs intake will remain unchanged. During the study period, patients will be forbidden to add any drugs other than study therapies without permission. During the 1–4 weeks of the treatment period, if the participant’s symptoms increase after the reduction of PPIs according to the study protocol and cannot be tolerated, participant can temporarily use almagate suspension or almagate chewable tablets and record the combined medication. During the treatment period of 5–6 weeks, if the participant is unable to tolerate the symptoms after stopping the acid suppressive drugs, participant will be terminated from the trial and recorded and will be treated with their original treatment therapy.

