### Timeline

The entire trial period will last 10 weeks (the treatment period is 6 weeks and the follow-up period will last 4 weeks). Participants will need to stop using drugs related to the treatment of NERD during pre-screening and screening, complete a physical safety examination, and sign an informed consent form. At baseline, participants will need to complete the first assessment and then randomly divided into an intervention group and a control group. During the treatment phase, TCM physicians will instruct the participants on how to take the therapy and then evaluate compliance and outcome indicators after 2, 4, and 6 weeks of treatment. The follow-up period will last 4 weeks after the end of treatment. Details are shown in Table 1.

**Table 1 Tab1:** Timeline of the trial

Study period										
	Screening	Baseline	Treatment						Follow-up	
Outcomes	Week -1	Week 0	Week 1	Week 2	Week 3	Week 4	Week 5	Week 6	Week 8	Week 10

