### Secondary outcomes

Secondary outcomes are the PPI withdrawal rate and symptoms recurrence rate, scales about minor symptoms, health-related quality of life, mental health, and TCM syndromes.PPI withdrawal rate and symptoms recurrence rate: During patient follow-up for the 4 weeks after the end of the treatment, according to the above scores, the number of recurrences and corresponding recurrence rates. The PPI withdrawal rate will calculated based on the number of people who no longer use PPIs at follow-up.Minor symptoms scale: Scoring the frequency and degree of clinical minor symptoms. For the frequency, 0 points indicates no symptoms, 1 points indicates < 1 day per week, 2 points indicates 1 day per week, 3 points indicates 2–3 days per week, 4 points indicates 4–5 days per week, and 5 points indicates 6–7 days per week. For the degree of symptoms, 1 points means no symptoms; 2 points means symptoms are mild; 3 points means symptoms are moderate, need to take medicine occasionally; 4 points means symptoms are severe, need to take medicine for long time; and 5 points means symptoms are very serious, and affecting daily life, need to take medicine for long time. Details are shown in Table 3.SF-36: As a concise health questionnaire, the SF-36 comprehensively evaluates the quality of life of the respondents from 8 dimensions including Physical Functioning (PF), Role-Physical (RP), Bodily Pain (BP), General Health (GH), Vitality (VT), Social Functioning (SF), Role-Emotiona (RE), and Mental Health (MH). It also contains another health dimension: Health Transition (HT), which is used to evaluate the overall change in health in the past year [30–33].PRO: This scale is for patients with FGIDs. It contains a total of 35 items, divided into 6 dimensions (regurgitation, dyspepsia, general condition, social function, defecation, psychology) to assess the influencing factors of chronic gastrointestinal diseases. Each item is graded on a 5-point scale, with a maximum of 4 points and a minimum of 0 points. The higher the score, the more severe the symptoms [34, 35].SAS: The SAS scale is a 20-item self-reported assessment device. Each question is scored on a Likert-type scale of 1 to 4 (based on the following replies: “a little of the time,” “some of the time,” “a good part of the time,” and “most of the time”). The total score is obtained by summing the assessment of the 20 items. The total score multiplied by 1.25 gives the standard score. A standard cutoff score of 50 is usually used to diagnose anxiety. The standard score ranges are 25–49 (normal range), 50–59 (mild anxiety), 60–69 (moderate anxiety), and 70 (severe anxiety) [36, 37].SDS: The Self-Rating Depression Scale (SDS) developed by Zung is a norm-referenced measure, used to screen adults for the potential presence of depressive disorders. The scale produces raw scores between 20 and 80; Zung recommended converting these to Index Scores (which ranged between 25 and 100) by the simple process of multiplying by 1.25. Zung’s recommended cut-off for identifying adults with depressive disorder was index scores of 50 and over [38]. We used in this study an index score of 53 (raw score 42); this was more appropriate for use with Chinese populations [39].GERD–HRQL: A total of 16 items are used to evaluate the symptoms of heartburn, regurgitation, and the effects of current medication on life. Each item is scored on a 6-point scale, from 0 to 5 points. A score of 0 indicates no symptoms, and a score of 5 indicates that symptoms are incapacitating when performing daily activities [40, 41].TCM syndromes scale: a 15-item scale based on *the Clinical Guideline of New Drugs for Traditional Chinese Medicine*. This scale evaluates the changes in TCM symptoms of the digestive tract and the whole body of the participants, including flatulence, stomachache, poor appetite, heartburn, belching, acid reflux, pharyngeal paraesthesia, thirst, distention in the lateral lower abdomen, fatigue, shortness of breath, unwillingness to speak, somatosensory heaviness, fear of cold, and loose stool. Each item is scored, with 1 being asymptomatic and 4 being severe. The higher the overall score, the more severe the overall symptoms [42].

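### The PPI withdrawal rate is counted in follow-up, where a permission-based drug restriction appears to apply with no rule for weeks 7–10, and participants terminated in weeks 5–6 have no stated place in it

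*Protocol article*

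**What the plan says.** The Cointerventions section of the protocol article states: "During the study period, patients will be forbidden to add any drugs other than study therapies without permission". It then gives two rules for symptoms that cannot be tolerated. In weeks 1–4, "participant can temporarily use almagate suspension or almagate chewable tablets and record the combined medication". In weeks 5–6 the participant leaves the trial and goes back to the treatment used before it. Nothing corresponding is given for weeks 7–10.

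Under Timeline, "The entire trial period will last 10 weeks", made up of six weeks of treatment and four of follow-up. Table 1 has a top heading of study period over columns that run from screening to weeks 8 and 10. Its cointerventions row is marked for weeks 1 to 6 only.

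Under Intervention group, "From week 5 to week 6, acid-suppressive drugs will be withdrawn, and only TCM granules will be administered". The Control group section applies the same step-down.

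Under Secondary outcomes, "The PPI withdrawal rate will calculated based on the number of people who no longer use PPIs at follow-up". No denominator is given. For missing data, the Dropout criteria section allows the last main efficacy value to stand as the final result, and the Statistical analysis section names carry-forward of the last record or multiple imputation, with intention-to-treat as the main approach.

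**The concern.** By week 5 every participant still on protocol has been taken off acid suppressants, so PPI use in follow-up can only be a restart. The Cointerventions section appears to regulate that restart, while the Secondary outcomes section counts it as the result. Whether a participant is on a PPI at week 8 or 10 can then depend on willingness to follow the restriction, and on whether someone at the centre gives permission, as well as on whether a PPI is needed.

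A second group matters as much. Participants who cannot manage without acid suppression in weeks 5–6 are terminated and returned to their earlier treatment. Eligibility requires more than 8 weeks of PPI treatment, so for them that treatment presumably includes a PPI. They are the clearest failures of withdrawal, but an endpoint defined only by status at follow-up does not say where they belong.

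The outcome is formally secondary. Even so, the Background and Discussion sections make reduction or withdrawal of PPIs one of the main reasons for the trial.

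**Working it through.** The plan gives no figure for the withdrawal rate, so there is none to reproduce. Its only computed figure, 174 participants, rests on an effective rate. It reproduces as (1.960 + 0.842)² × (0.9×0.1 + 0.7×0.3) / (0.20 − 0.02)² = 72.67 per arm, and 72.67 × 1.2 = 87.2. It is used below only for the arm size of 87.

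**Step 1: does the restriction reach follow-up?** The general sentence speaks of the study period. The two symptom rules that follow it use the narrower term treatment period. Table 1 uses study period as the heading over all columns, including weeks 8 and 10. The plain reading is that the restriction runs to week 10. This is an inference, because the sentence does not name follow-up.

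**Step 2: what governs a PPI restart in each window?**

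| Window | Rule for intolerable symptoms | Cointerventions recorded (Table 1) | Enters the withdrawal rate? |
|---|---|---|---|
| Weeks 1–4 | Temporary almagate | Yes | No |
| Weeks 5–6 | Termination, return to earlier treatment | Yes | Not stated |
| Weeks 7–10 | None; general restriction, permission possible | No | Yes |

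The one window that supplies the endpoint is the one with neither a symptom rule nor scheduled recording of added drugs.

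**Step 3: effect of the restriction on the contrast.** Let *a* be the share of an arm that needs a PPI in follow-up, and *c* the share of those who stay off it because of the restriction or a refused permission. The observed withdrawal rate is 1 − *a*(1 − *c*). With the same *c* in both arms, the difference is (a_control − a_granules)(1 − *c*), so the true difference shrinks by the factor (1 − *c*). The needs of 50% (control) and 30% (granules) are assumptions, not figures from the protocol. Power is for a two-sided 5% test with 87 per arm.

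| *c* | Control | Granules | Difference | Power |
|---|---|---|---|---|
| 0 | 50% | 70% | 20 points | 77% |
| 0.25 | 62.5% | 77.5% | 15 points | 58% |
| 0.5 | 75% | 85% | 10 points | 38% |
| 0.75 | 87.5% | 92.5% | 5 points | 19% |
| 1 | 100% | 100% | 0 | no contrast |

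With higher assumed needs of 68% and 48%, power at *c* = 0, 0.25, 0.5 and 0.75 is 77%, 51%, 31% and 15%, so the pattern does not hinge on the level chosen. The document does not fix *c*.

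**Step 4: placing the participants terminated in weeks 5–6.** Let *t* be the share of an arm terminated then, and *r* the share of the rest who restart a PPI. The withdrawal rate is:

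- counted as failures: (1 − *t*)(1 − *r*)
- left out: 1 − *r*
- carried forward as off PPIs: *t* + (1 − *t*)(1 − *r*)

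The first and third differ by exactly *t*. If, as an assumption, the plan's whole 20% attrition allowance were such terminations, that is 20 points in an arm (0.20 × 87 = 17.4 participants).

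Now suppose granules reduce terminations (t_granules < t_control) and *r* is equal in the two arms. Granules minus control is then (t_control − t_granules)(1 − *r*) under the first rule, zero under the second, and −*r*(t_control − t_granules) under the third. Leaving these participants out hides the benefit, and carrying them forward can reverse its sign.

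**The case against.** The best defence is that the co-medication rules end with treatment. Every specific rule under Cointerventions concerns weeks 1–6, and Table 1 schedules both compliance and cointerventions for those weeks only. The restriction is also conditional: it allows drugs with permission and exempts study therapies, and PPIs belong to the step-down regimen. By counting who is off PPIs at follow-up, the endpoint presupposes that some may be on them. Who gives permission, and on what grounds, may stand in the full protocol. Under the present wording, a participant using a PPI at follow-up is already not counted as withdrawn, permitted or not.

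Much of this stands, and it limits the point. It does not remove it. If the restriction ends at week 6, the article states no rule at all for the weeks that yield the endpoint. The step-down contains no PPI after week 2, so the exemption for study therapies does not clearly cover a later restart. Nor does the existing definition settle the terminations in weeks 5–6. An intention-to-treat analysis suggests that these participants stay in the denominator, but it does not say what status they carry.

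A reader might infer more in three ways, and the documents do not support these:

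- *The endpoint measures only obedience, with a rate of 100% in both arms.* This needs a ban to week 10, permission never given and full adherence. The protocol states none of these, and permission may well follow symptoms.
- *Participants who restart a PPI are dropped for poor compliance.* The Compliance section defines compliance by the ratio of doses taken to doses due, and no study dose is due in weeks 7–10.
- *The 68% recurrence cited in the Background gives the size of the problem.* That figure is symptom recurrence in another study, not PPI resumption, and setting it against 100% only compares two hypothetical extremes.

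Differences between centres in granting permission are also not a bias between arms in themselves. Practitioners are blinded and allocation is blocked within centre, so the expected effect is dilution.

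**Conclusion.** The point holds in a limited form. On the plain reading of Table 1, the drug restriction extends into the weeks where PPI use is an outcome, and no symptom rule is stated for those weeks. The withdrawal rate is therefore partly confounded with compliance and undefined permission. The main consequence is dilution by the factor (1 − *c*), assuming *c* is the same in both arms. On the assumed needs of 50% and 30%, a *c* of 0.5 halves a 20-point difference and takes power from 77% to 38%. The actual size cannot be derived from the document.

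The unstated place of participants terminated in weeks 5–6 is the more serious part, because it can change the direction of the comparison as well as its size. It does not depend on how far the restriction reaches. As a secondary outcome tied to a declared aim, the rate should be put right, but the primary analysis is not affected.

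**What to change.** 1. Reconcile the Cointerventions and Secondary outcomes sections so that one stated rule on acid-suppressive use in weeks 7–10 applies in both arms and all six centres. Its clinical content is for the investigators.
2. Define the PPI withdrawal rate over all randomised participants. Count as not withdrawn anyone who returns to a PPI after the scheduled withdrawal and up to week 10, with or without permission, including those terminated in weeks 5–6 who go back to a PPI. Do not carry an off-PPI record forward for them.
3. Extend the cointerventions row of Table 1 to weeks 8 and 10, so that the data for the endpoint are collected on schedule.

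The cost is a short amendment, which needs ethics re-approval under the protocol's own terms, and one added item at two existing visits. The reported withdrawal rate may be less favourable. The conduct rule and the recording have to be settled before the follow-up data are collected, since an analysis plan cannot supply them afterwards.
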